#### Statistical analysis plan

Statistical analyses will be performed with R and SPSS software. Demographic, behavioural and other descriptive variables will be represented as means and SDs or percentages where appropriate. Analysis of variance, t-tests or χ^2^ tests will be used to determine differences between groups (in brain responses, eg, differences between responses to food and non-food pictures, differences in responses between different food categories, as well as differences in brain responses between the second and third trimester of pregnancy and between NW women and OW/OB). Paired t-test will be used to determine within-subject differences between both timepoints (second and third trimester). Regression analyses will be used to model the relationship between predictor variables and outcomes (such as between brain responses to food viewing with intuitive eating and metabolic health). Associations between objective eating behaviour measures and neurobehavioural responses to food cues will be evaluated using correlation and multivariable regression analyses. Specifically, we will examine whether eating onset latency, eating duration and eating rate are associated with EEG responses to food images and behavioural performance on the Go/NoGo task, and whether these relationships differ according to the BMI group. We will also investigate the impact of covariates such as maternal age, GA, prepregnancy BMI on outcomes and adjust for them when necessary.

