## Aims

The overall aim of this study is to investigate brain responses to food viewing in the beginning of the second and the third trimesters of pregnancy and their relationship with metabolic health. We will investigate this in pregnant individuals with NW and with OW/OB, which are at higher metabolic risk.

Primary objectives:To investigate differences in brain and behavioural responses to food pictures of varying fat and carbohydrate content: high-fat/high-carbohydrate (HFHC), high-fat/low-carbohydrate (HFLC), low-fat/high-carbohydrate (LFHC) and low-fat/low-carbohydrate (LFLC) during pregnancy, in women with and without OW/OB.To investigate the relationships between brain responses to food pictures as measured by electroencephalography (EEG) and the behavioural responses to food cues measured with a smartphone-based Go/NoGo task in these individuals.Secondary objectives in the same population:To determine the relationships between brain responses to food pictures and different emotional states and stress levels.To investigate differences in brain and behavioural responses to food and non-food pictures.To investigate longitudinal changes in brain and behavioural responses to food pictures of varying fat and carbohydrate content from early to late pregnancy.To investigate the cross-sectional and longitudinal relationships between brain responses to food viewing with eating behaviour, metabolic health and mental health during pregnancy.

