#### Behavioural task during EEG recording

Participants will complete a speeded two-alternative forced choice discrimination task across the four previously described blocks of trials, lasting approximately 13 min in total. During this task, participants will indicate whether each cue presented represents a food or a non-food item by pressing a button on a response box with their dominant hand (button ‘1’ for food pictures, button ‘2’ for non-food object pictures). The block order will be randomised across participants.

The experimenter will first provide a detailed explanation of the task, followed by a brief practice session with seven food and three non-food pictures to familiarise participants with the procedure. Additionally, short on-screen instructions will be presented at the start of each block. Participants will be encouraged to take brief breaks between blocks to reduce fatigue.

Behavioural measures will include the mean response time (RT) (in milliseconds) for correctly identified food and non-food pictures, as well as for each food category. Accuracy (%) will be calculated as the proportion of correctly responded trials. The same selection of food cues will be shown on both visits.

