#### Go/NoGo gamified task

A specific smartphone will be provided to complete a gamified Go/NoGo task lasting a total of approximately 15 min. Participants will be asked to complete this task 10 times in total; once during each of the visits and nine additional times per visit at home. This task will include 24 randomised food cues of varying fat and carbohydrate content (see section ‘Food categories’) circled in green (Go cues), and 4 randomised object cues circled in red (NoGo cues). In total, there will be 70% of Go cues and 30% of NoGo cues. Participants will complete multiple runs of the task each day until they fulfil a daily objective, receiving intermediate scores after each run, and a final score when the objective is achieved.

Before the first game, participants will be asked in the app to answer a liking questionnaire (Visual Analogue Scale (VAS) from 0=strongly dislike to 100=strongly like), where they will rate food images presented during the Go/NoGo task. Before each task, participants will be asked to answer a questionnaire regarding their current mood (A-MMS), current level of perceived stress (single item) and current level of hunger (single item).

During the task, participants will be instructed to respond as fast as possible to the food cues (Go trials) by sliding the image downward with their finger, while withholding their responses to the non-food cues (NoGo trials). If participants respond to a food cue on time (Hit) or correctly withhold their response to an object cue (correct rejection, CR), positive green feedback will be displayed. If participants fail to respond to a food cue within 1.5 s (Miss) or respond to an object cue (false alarm, FA), negative red feedback will be displayed.

As part of the task’s gamified design, and to maintain engagement and adherence, participants who will correctly respond to food cues but exceed the reaction time threshold (RTT, 725 ms) will receive a negative ‘Late’ feedback, while a ‘Down’ feedback will be displayed if the food cues are not dragged to the bottom of the screen.

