##### Global field power

To quantify the differences between groups and categories in strength of the VEPs, GFP will be calculated for each participant and food category. GFP is the spatial SD of the electric field of all electrodes and is used to quantify response strength at each time point, considering data from all electrodes simultaneously.^55^ Mean GFP within each time window, based on the abovementioned topographic clustering analysis, will be analysed using rmANOVAs with fat and carbohydrate as within-subject factors and group as the between-subject factors. Significant interactions will be adjusted for multiple comparisons. These analyses will be performed using SPSS.

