##### Analysis of the gamified Go/NoGo task

Raw data from the gamified Go/NoGo task will be collected through The Diner smartphone application and preprocessed using the Diner Data Processor, a Matlab-based processor. For each participant, all raw data files will be extracted directly from the smartphone.

Raw log files will then be analysed and transformed into an Excel dataset for each participant through the processor.

Behavioural data will be imported from Excel files to R running or RStudio will be used^59^ and packages from tidyverse.^60^ Mean RTs will be calculated from the correct responses (Hit trials) for each food item, food category, participant and training day. The food category mean RTs will be calculated by averaging the RT of all items within each food category for each participant and day. Overall RT to food cues will be computed by averaging across all food categories, participants and day. In addition, accuracy measures, including the percentage of correct responses, number of errors, and inhibition error rates (FA/CR+FA)*100, will be computed per participant and per day. Further analyses will include modelling using repeated measures analyses of each day.

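### No stated test asks whether change across pregnancy differs by food category or BMI group: the within-subject test is a paired t-test, and the one model with listed factors has no visit term

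*Protocol article*

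**What the plan says.** All references are to the protocol article.

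- **Aims, secondary objectives.** The longitudinal objective is "To investigate longitudinal changes in brain and behavioural responses to food pictures of varying fat and carbohydrate content from early to late pregnancy". It applies to the same population as the primary objectives, that is, women with and without overweight or obesity.
- **Statistical analysis plan.** The within-subject test is named: "Paired t-test will be used to determine within-subject differences between both timepoints (second and third trimester". The same section lists ANOVA, t-tests or χ² tests for several comparisons, among them "differences in brain responses between the second and third trimester of pregnancy and between NW women and OW/OB". It introduces these as differences between groups and gives no visit factor or interaction.
- **Global field power.** The analysis is by "rmANOVAs with fat and carbohydrate as within-subject factors and group as the between-subject factors". Visit is not among the factors.
- **Analysis of the gamified Go/NoGo task.** "Further analyses will include modelling using repeated measures analyses of each day". No visit, category or group terms are given.
- **Behavioural task during EEG recording.** "The same selection of food cues will be shown on both visits".
- **Go/NoGo gamified task.** The task is done once at each visit and "nine additional times per visit at home".
- **Sample size calculation.** 94 women (47 per group), anticipated dropout of 10–20%, and about 37 per group expected with valid data at the second visit.

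**The concern.** The longitudinal objective is framed by food category, and the cohort is built to compare two BMI groups. A paired t-test on two occasions asks only whether a mean changed. It does not ask whether the change was larger for high-fat than for low-fat pictures, or larger in one BMI group than in the other. If neither comparison has a stated test, the easy substitute is to run paired tests within each category or group and compare which are significant. That does not test a difference in change, and it can yield a claim that one group changed and the other did not when both changed equally.

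Two further matters bear on the same analysis. A paired test leaves out every woman without a valid second visit. The visit contrast also carries any practice effect, because EEG pictures are reused and the Go/NoGo task is repeated many times before the second visit.

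**Working it through.** **1. The hypotheses side by side.** Let D be a woman's visit 2 value minus her visit 1 value for a given food category.

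- Paired t-test: mean(D) = 0, for one category or averaged over categories.
- Visit × fat: mean(D for high-fat − D for low-fat) = 0.
- Visit × group: mean(D in OW/OB) − mean(D in NW) = 0.

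The first is stated. The second and third are not. The listed rmANOVA tests fat, carbohydrate, group and their interactions, without D entering.

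**2. The plan's own sample size.** The stated f = 0.34 for fat × group gives d = 2 × 0.34 = 0.68. A two-sided two-sample t-test at alpha 0.05 and 80% power then needs 34.9, so 35 per group, as stated. This figure is for a fat × group effect, not for change between visits. The expected 37 per group at visit 2 corresponds to 20% dropout alone (47 × 0.80 = 37.6) and is used below as the plan's figure.

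**3. What 37 per group can detect for change** (two-sided 0.05, 80% power, t-based, in SDs of the change score).

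- Overall change, 74 pairs: about 2.80/√74, t-based 0.33 SD.
- Difference in change between groups, 37 per group: about 2.80 × √(2/37), t-based 0.66 SD.

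The group comparison of change is therefore much less sensitive than the overall change.

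**4. Women lost from a paired test.** Complete pairs: 94 × 0.90 = 84.6 and 94 × 0.80 = 75.2, so 9–19 women are lost.

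*Precision cost.* Assume equal variance at both visits, dropout completely at random with proportion q, and within-person correlation ρ (assumed, 0.3–0.9). The variance of mean change from a likelihood model on all women, relative to complete pairs, is 1 − q(1 − ρ)/2.

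| q | ρ = 0.3 | ρ = 0.9 |
|---|---|---|
| 0.10 | 0.965 | 0.995 |
| 0.20 | 0.930 | 0.990 |

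The gain is 0.5–3.5% at 10% dropout and 1–7% at 20%.

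**5. What comparing separate p-values would do.** This is an illustration, because the plan does not describe the step. Suppose both groups truly change by the same standardised amount dz (assumed). With 37 pairs per group and power p for each paired test, the chance that exactly one group is significant is 2p(1 − p).

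| dz | p | exactly one significant |
|---|---|---|
| 0.3 | 0.43 | 49% |
| 0.4 | 0.66 | 45% |
| 0.5 | 0.84 | 27% |
| 0.6 | 0.94 | 11% |
| 0.8 | 0.997 | 0.6% |

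Pooled over 74 pairs at dz = 0.4, the paired test has 92% power for overall change.

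**6. Practice.** One Go/NoGo session at visit 1 plus nine at home makes ten before visit 2. A small simulation (200 runs, 94 women, 20% dropout, correlation 0.5) used an assumed practice shift of 0.3 SD and no pregnancy effect. The paired t-test and the mixed model both estimated a change of 0.30. A shift δ common to both groups, or to all categories, cancels in the interaction contrasts (δ − δ = 0). A shift that differs between them does not.

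**The case against.** The strongest reply is that the paired t-test is not the only method named. ANOVA is listed for category, trimester and group differences together, and the Go/NoGo section promises repeated-measures modelling by day. Paired tests on category contrasts, or group t-tests on change scores, would fit the text and answer parts of the objective. The objective does not say in so many words that change will be compared between BMI groups; that rests on the two-group population. It is also secondary, and the article calls several analyses exploratory. Finally, a condensed article may leave a factor list to a fuller document.

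Much of this stands, and it rules out saying that the plan cannot answer its objective. What remains is narrower. The article's own analysis section selects a test for within-subject change, and it lists factors elsewhere when it has chosen them. The selected test does not match an objective worded by fat and carbohydrate content, and the alternatives that would match are not stated.

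Three stronger readings are tempting and not supported:

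- **A false difference between groups in 42–45% of studies.** This needs dz = 0.4 (37–40 pairs per group) and a by-group comparison of p-values. The documents give neither, and the rate runs from 0.6% to 49% over dz 0.3–0.8.
- **A serious loss of data.** 9–19 women sounds large, but the precision cost is small if dropout is completely at random. An rmANOVA on visit 1 alone would keep these women. Bias from outcome-related dropout cannot be sized from the documents.
- **Practice as a fault of the paired t-test.** It comes from the design, and a mixed model gives the same biased visit effect. The statement about reused pictures also concerns the EEG task, not Go/NoGo.

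**Conclusion.** The point holds as a mismatch between one secondary objective and its stated analysis. No visit × category or visit × group test is specified, so whether change differs by fat/carbohydrate category or BMI group is not directly tested as the plan is written. The primary analyses of category and group differences are not affected.

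The main gain from a change is a stated test of the interactions. The smaller gains are keeping 9–19 women in the analysis and relying on a weaker missing-data assumption; the 0.5–7% precision figure assumes dropout completely at random, equal variances and correlations of 0.3–0.9. Even with the right model, the group difference in change is detectable only at about 0.66 SD with 37 per group, so a null result there should be read with care.

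Separately from the choice of test, the overall visit effect cannot be attributed to pregnancy stage alone. Pictures are reused in the EEG task, Go/NoGo is practised repeatedly before visit 2, and there is no non-pregnant comparator.

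**What to change.** - **Model.** For the longitudinal objective, replace the paired t-test for EEG measures and Go/NoGo reaction time with a linear mixed model with visit × fat × carbohydrate × group and a participant random effect. Let the visit effect also vary between participants; otherwise the four category values per visit are treated as independent evidence of change. Include all women with any valid visit.
- **EEG time windows.** Derive them from evoked potentials pooled over both visits, so that the same window is compared.
- **Claims.** Base any statement that change differs by category or group on the visit interactions, not on separate within-group or within-category p-values.
- **Practice.** Report the overall visit effect as not separable from practice. Adjusting for cumulative session number is not a remedy, because session number is nearly determined by visit.

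The cost is analysis wording. R and SPSS are already named, and data collection does not change. The downside is a more complex model to fit and report.

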### Study population and eligibility criteria

A total of 94 participants with valid data for the primary outcomes will be included. The study will include two groups of participants based on their prepregnancy BMI, one including individuals with NW and a second group of individuals with OW/OB. Recruitment will be done through flyers in the Lausanne University Hospital and various ambulatory regional hospital clinics as well as private obstetrics and gynaecology practices in the canton of Vaud. Eligibility will be determined during recruitment using a screening questionnaire before enrolment. Participants will self-report all inclusion and exclusion criteria. For both groups, inclusion criteria will include pregnant women with GA between 12 and 16 weeks, aged ≥18 years, and willingness and ability to provide signed informed consent. Additional inclusion criteria for the NW group will be: prepregnancy BMI <25 kg/m^2^, no restrictive diets during pregnancy, no weight changes exceeding 5 kg in the past 5 years (excluding pregnancy), and weight gain within 2 kg during the first trimester, in accordance with the National Academy of Medicine recommendations at the time of inclusion.^27^ Inclusion criteria for individuals in the OW/OB group will be prepregnancy BMI ≥25 kg/m^2^.

Exclusion criteria will include pre-existing diabetes, a diagnosis of an eating disorder (eg, anorexia nervosa, bulimia nervosa or binge-eating disorder), vegetarian or vegan diet (to ensure familiarity and exposure to all food categories), uncontrollable nausea and vomiting during the first trimester of pregnancy, history of bariatric surgery, participation in an intervention study, diagnosed mental illness or use of medication to treat psychiatric disorders, as well as active suicidal thoughts and having an implanted cardioverter-defibrillator.

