### Data management and statistical analyses

#### Sample size calculation

The sample size estimation was informed by previous EEG studies of similar design outside of the perinatal context,^23
28
48^ as well as internal pilot data from our group. For EEG outcomes, preliminary data from our previous study (CER-VD 2021-01976) showed a significant fat x group interaction in global field power (GFP) (ηp²=0.103, F(1,37)=4.237, p=0.047; Cohen’s f=0.34). Power analysis assuming an alpha level of 0.05 and 80% power indicated that 35 participants per group were needed. For the Go/NoGo smartphone task used in a different context, pilot data demonstrated group differences in RTs of 550 ms±63 in women with NW and 450 ms±63 in women with OW/OB, at least eight participants per group would be required to detect significant differences in RT assuming an alpha level of 0.05 and 80% power.

Participants diagnosed with GDM at the second visit (approximately 16%) will be excluded in sensitivity analyses. To account for these exclusions and an additional anticipated dropout of 10%–20%, a total of 94 participants (47 per group) with valid data will be recruited. This is expected to result in approximately 37 participants per group at the second visit with valid data, corresponding to the highest requirement derived from our calculations.

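### For primary objective 2 (EEG against Go/NoGo response), the plan does not require BMI group in the model and leaves adjustment for prepregnancy BMI to an undefined condition

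*Protocol article*

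**What the plan says.** The Aims section of the protocol article lists as its second primary objective the relationship between EEG responses to food pictures and "the behavioural responses to food cues measured with a smartphone-based Go/NoGo task in these individuals". Under Study population and eligibility criteria the sampling is stratified: "The study will include two groups of participants based on their prepregnancy BMI". Sample size calculation sets the numbers: "a total of 94 participants (47 per group) with valid data will be recruited", expected to leave "approximately 37 participants per group at the second visit with valid data".

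The Statistical analysis plan section has no model specific to objective 2. It has the general statement "Regression analyses will be used to model the relationship between predictor variables and outcomes", illustrated with intuitive eating and metabolic health. Correlation and multivariable regression are named for the measures from the eating recognition device (onset latency, duration, rate). Only for these does the section commit to examining differences between BMI groups; Snack and objective eating behaviour repeats that commitment. The section ends with a covariate rule: maternal age, gestational age and prepregnancy BMI are given as examples of covariates whose influence will be studied, and the authors will "adjust for them when necessary". The Abstract says that regression models are adjusted for potential confounders, without naming group or BMI.

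**The concern.** When a sample is built from two groups, any two variables that both differ between the groups are correlated in the pooled data, even if they are unrelated within each group. The planning figures expect such differences on both sides of objective 2: an EEG effect by group, and reaction times of "550 ms±63 in women with NW and 450 ms±63 in women with OW/OB". An unadjusted pooled slope would then partly restate the group contrast of objective 1 and could be reported as a separate brain–behaviour link.

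The variable that defines the sampling is here an optional adjustment with no stated trigger, while differences by BMI group are firmly planned for the eating-device associations, which are secondary. At stake is whether a positive finding on a primary objective can be told apart from a consequence of the design.

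**Working it through.** **Inputs (protocol article, Sample size calculation)**
- EEG: fat × group interaction in global field power, F(1,37) = 4.237, ηp² = 0.103, f = 0.34.
- Go/NoGo reaction time: means 550 and 450 ms, SD 63.
- 47 per group recruited, about 37 per group at visit 2 (taken as stated), alpha 0.05. Sidedness is not stated; two-sided is assumed.

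**Reproducing the plan's figures**
- ηp² = 4.237/(4.237 + 37) = 0.103; f = √(0.103/0.897) = 0.34; d = 2f = 0.68. A two-sample t-test at 80% power needs 34.9, so 35 per group. Stated: 35.
- d = 100/63 = 1.587. The same test needs 7.33, so 8 per group. Stated: 8.

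Both agree, so these effect sizes are the ones the plan used.

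**Pooled correlation induced by group**

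With equal groups, each variable's correlation with group is d/√(d² + 4):
- EEG: 0.68/√(0.462 + 4) = 0.322
- Reaction time: 1.587/√(2.519 + 4) = 0.622

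With zero within-group correlation, the pooled correlation is the product, 0.322 × 0.622 = 0.20 in absolute value.

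**How often it is significant**

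Fisher z check: atanh(0.20) = 0.203.
- 47 per group: 0.203 × √91 = 1.93, so the chance of exceeding 1.96 is about 49%.
- 37 per group: 0.203 × √71 = 1.71, about 40%.

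Simulation with zero within-group correlation (20,000 datasets for the unadjusted and group-term rows):

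| Model | 47 per group | 37 per group |
|---|---|---|
| Unadjusted, pooled | 51% | 41% |
| Continuous BMI added when it predicts the outcome | 11–14% | 9–13% |
| BMI group as a term | 5.0% | 4.9% |

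The middle row rests on assumptions that are not in the documents. NW BMI is normal with mean 22 and SD 1.7, held to 18.5–24.9. OW/OB BMI is 25 plus a gamma variable with shape 2 and scale 2.5. The group effect is a step at the cut-off. BMI enters when its own p-value for the outcome is below 0.05. The ranges reflect which of the two measures is taken as the outcome. A linear BMI term does not fully absorb a step, so some inflation remains.

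**Sensitivity, unadjusted, 47 per group**
- Reaction-time d = 1.587, with EEG d of 0, 0.2, 0.4, 0.5, 0.68, 0.8: 5%, 9%, 22%, 31%, 51%, 63%.
- EEG d = 0.68, with assumed reaction-time d of 0.2, 0.5, 0.8: 6%, 11%, 21%.
- With a group term the rate is about 5% throughout. Under the conditional BMI rule with smaller effects it is 5–11%.

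**The case against.** A reader might infer that the plan analyses objective 2 by pooled regression or correlation with group left out. The documents do not say so. The general regression sentence lists no terms, correlation is named for the eating-device measures, and the covariate rule names prepregnancy BMI. If that rule were applied, most of the inflation would go. This objection stands, and it limits the point to what the plan fails to require.

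The 51% is also not a forecast for this study. The d of 0.68 belongs to a high-minus-low-fat contrast in global field power, not to latency, duration, topography or source activity. The d of 1.59 is for overall reaction time, from pilot use of the task in a different context. The plan does not say that these two scores will be paired. This stands too, so the rate must be read with the sensitivity range.

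Another objection is that conditioning on group is a choice of estimand: the Aims ask about relationships in these individuals, and an association across BMI does exist if both measures differ by BMI. That is fair. It is a reason to say which association is primary and to keep the pooled one as description; it does not justify leaving the choice until the data are seen.

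Finally, a condensed article may leave model terms to a full analysis plan that is not shown. Mere absence of terms would be no finding. But the article does state a rule for adjustment, and that rule is discretionary for the variable that defines the sampling.

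**Conclusion.** The point holds in limited form. For primary objective 2 the plan does not require BMI group and makes adjustment for prepregnancy BMI conditional on an undefined judgement, so an association created by the two-group sampling is not excluded. At the plan's own pilot effects, with no within-group association, the unadjusted analysis is significant in about 51% (47 per group) or 41% (37 per group) of studies, conditional adjustment for continuous BMI in roughly 9–14%, and a group term in about 5%. These rates need a group difference in both measures and fall to 5% if either is zero. The middle figure also depends on the assumed BMI distributions and the step-shaped effect.

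A reader might carry the argument over to the models for adiposity and HbA1c. The documents do not support that. They give no group effect for either, so no size can be calculated. Adiposity is also close to what defines the groups, so conditioning on group there could remove variation the study wants to examine.

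This should be changed, but it does not threaten the study.

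**What to change.** In the Statistical analysis plan section, state that models for primary objective 2 always include BMI group as a fixed term. The common within-group slope of Go/NoGo response on EEG response is the primary estimate. A group × EEG term tests whether slopes differ between NW and OW/OB. The unadjusted pooled association is reported as descriptive only. Do not make the group term mandatory in the adiposity or HbA1c models.

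The cost is a sentence or two of wording and one degree of freedom for the group term (one more in the model that tests the interaction). Any part of the association that runs through group is no longer counted in the primary slope, but it remains visible in the descriptive pooled estimate.
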